# 6.0 STUDY OUTCOMES

The main outcome of the study will be progression of HIV disease (Table 6). The time of the main outcome will be defined as the interval from enrollment until an outcome event first occurs. In the case of CD4+ counts, when a subject has met the criteria for primary outcome, the date of the first of two CD4+ counts < 250/ml will be used. Secondary outcomes will be response to antituberculosis therapy and safety.

For analysis, a Clinical Review Committee, chaired by the PI or designee, will be formed at the start of the study to review and classify all outcomes of the trial in a blinded way. Outcomes will be recorded on standard data collection forms for entry into an outcomes database. For clinical care on-site, medical officers will operationalize outcome definitions so that patients may be treated in a timely manner.

Table 6. Summary of Study Outcomes

| Study Aim | | Measurement |
| --- | --- | --- |
| Primary Objective | Aim |
| HIV Disease Progression | 1 | Time interval from enrollment until 2 CD4+ count < 250/*µ*L within a 3 month time period , rate of decline in CD4+ T cell counts  - Development of AIDS-defining condition (WHO Staging System; not including recurrent TB)  - Definitive diagnosis of a severe bacterial infection that meets WHO Stage 3 criteria  - Death |
| Secondary Objectives |  |  |
| Response to Antituberculous therapy  Safety | 2  3 | MTB Sputum Conversion  Cure of active TB  TB Treatment failure  TB Relapse  Grade III/IV adverse reactions  Paradoxical reactions  HIV Drug resistance |

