### **5.2.3 Blinding**

The ARV intervention will be open-label. In the proposed design, study subjects and physicians alike will be aware of the treatment assignment at the initiation of the intervention. The initiation of the intervention will occur between 2, and 4 weeks following initiation of standard anti-TB treatment. A placebo controlled design was not chosen because of ethical concerns and the sensitivities regarding placebo trials in the study population.

To address detection and reporting bias, we will use a reproducible, laboratory-based endpoint based on CD4+ measurements that is not subject to interpretation by investigators or subjects. Laboratory specimens will be identified by study subject ID numbers. Laboratory staff performing safety, microbiological and immunologic assays will be blinded to treatment arm assignment. Clinicians will be masked to treatment assignment during chest X-ray reading.

To minimize bias further, the frequency and duration of follow-up will be similar in both study arms. Outcome data will be collected and recorded in a standard manner for all study subjects. A Clinical Review Committee composed of senior level faculty at Case Western Reserve University, University California San Francisco, Makerere University review and classify all study outcomes (Table 6) in a blinded manner. Losses to follow-up will be recorded; reasons for the loss to follow-up will also be recorded. The potential bias from unbalanced treatments of intercurrent infections will be minimized by the use of a standard protocol for the treatment of these conditions.

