Patients who have one or more of these contraindications to starting antiretroviral therapy will be evaluated and treated for the conditions causing abnormal values. Patients will be started on antiretroviral therapy once the acute condition has resolved. For patients who have persistent abnormal values that are attributed to progressive HIV infection, they will be eligible to start antiretroviral therapy with an appropriate regimen. Patients who are eligible to start antiretroviral therapy formally enter Step 3 and will have a pre-ARV baseline assessment, which includes (see Appendix I, Step 3):

1. HIV RNA Roche Amplicor
2. Quality of life assessment
3. Plasma storage
4. PBMC storage/ immune function (Flow cytometry to assess cell surface activation markers, EliSpot to assess CD4 and CD8 T cell specificity to HIV and microbial peptides, Whole blood assays to determine antigen specific response to HIV and microbial antigens)

Patients who satisfy all indications for therapy and safety evaluations will be started on ARV therapy. Once starting ARV treatment, patients will be followed per schedule of evaluations, Appendix I, Step 3.

If a patient is taking punctuated therapy at the time of a primary outcome, they will be evaluated for virologic failure (Section 8.1.3). Patients will be evaluated to determine whether a new protocol indicated regimen should be initiated or whether current regimen should be held, discontinued, or re-started. See section 5.2.1.4 and 8.1.4.

Patients who are not eligible for starting antiretroviral therapy at the time of the primary outcome will be reassessed in a month. If the contraindications for antiretroviral treatment have resolved, the patient will enter Step 3 as described above. If contraindications to antiretroviral treatment persist, then the patient will be followed and assessed for ARV safety eligibility monthly or as clinically indicated. Patients will be reassessed for contraindications at these monthly visits, or sooner if clinically indicated. If a patient is found eligible for antiretroviral therapy at any of these follow-up visits, then the patient will enter Step 3 as described above.

Patients will be started on self-administered ARV therapy in accordance with Ugandan National Treatment Guidelines, or as directed by the Principal Investigator or designee.

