#### **6.3.1.1 Procedures for Reporting Serious Adverse Experiences**

All serious adverse experiences as defined in Section 6.3, occurring in study subjects during the course of the study must be reported promptly to the Principal Investigator, the Data Coordinating Center at UCSF, the TB Research Unit Coordinating Center at CWRU and the Study Sponsor (DAIDS) at the following address:

The DAIDS Regulatory Compliance Center (RCC)/Safety Office,

e-mail address: [contact],

[contact],

[contact].

The study site physician also is responsible for reporting any SAE arising during the conduct of the study to the local IRB.

Requirements for adverse experiences requiring reporting are listed and summarized in the following flow diagram:

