#### **8.1.4.2 General Guidelines for Holding, Discontinuing, and Re-starting Study Antiretroviral Drug**

Certain events or conditions, described above, may require that study physicians either hold or discontinue study drugs. The decision to hold a patient’s antiretroviral medication during the study will be the responsibility of medical officers, their physician supervisors and study investigators. Decisions to discontinue or re-start study drug must be presented and discussed with the U.S. or on-site Principal Investigator, or their designee.

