##### 8.1.4.2.3 Criteria for Re-starting Antiretroviral Therapy

The decision to restart antiretroviral therapy will depend on the type of adverse event and the study drug. Three general situations will arise:

1. If a patient develops intolerance to a medication as evidenced by an adverse event, then the medication(s) may be re-started once the adverse event has resolved or subsided to a grade II reaction or less. In this setting, the offending medication may be restarted under close supervision that involves direct observation of the initial dose and frequent clinical and laboratory monitoring thereafter.
2. If a patient develops an allergic or hypersensitivity reaction to one or more of the antiretroviral medications, the drug(s) must be discontinued and NOT be re-started. See comments below regarding ABC.
3. If a patient develops an adverse event to a medication other than an antiretroviral medication, then the antiretroviral medications may be re-started under careful clinical supervision.

Study medical officers and physicians have the option of substituting a protocol-approved antiretroviral medication when clinically indicated instead of re-starting medication.

*ABC – Re-Starting Therapy*

Although patients may develop allergic reactions to any medication, special rules about stopping and re-starting ABC are needed because of ABC HSR.

If the diagnosis of ABC HSR is made, then the ABC must be discontinued. If ABC was held for evaluation of an adverse event, and that adverse event is clearly ascribed to another cause, then medical officers may re-start ABC under direct observation of medical personnel and close follow-up. If ABC is to be re-started under these circumstances, the drug must be restarted by the site principal investigator or his physician designee after discussion of the risks and benefits of restarting the drug with the subject. Reintroduction of the drug must occur in Mulago Hospital where the subject can readily access medical care.

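### The protocol promises blinded outcome classification but lets the committee be chaired by the PI or a designee, a role that can learn individual patients' arms from ARV decisions and SAE reports

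*Protocol*

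**What the plan says.** Section 5.2.3 makes the ARV intervention open-label: "study subjects and physicians alike will be aware of the treatment assignment at the initiation of the intervention". Among the measures against bias it lists a committee of senior faculty from three universities that will "review and classify all study outcomes (Table 6) in a blinded manner". Section 6.0 repeats the promise, saying the committee exists "to review and classify all outcomes of the trial in a blinded way", and in the same sentence describes it as "a Clinical Review Committee, chaired by the PI or designee". Sections 6.2.6 and 6.3.3 restate the blinding for recurrent TB and for paradoxical reactions.

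Elsewhere the PI role is tied to individual patients:

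- Section 8.1.4.2: "Decisions to discontinue or re-start study drug must be presented and discussed with the U.S. or on-site Principal Investigator, or their designee".
- Section 8.1.4.2.3, on abacavir held for an adverse event that proves to have another cause: "the drug must be restarted by the site principal investigator or his physician designee".
- Section 6.3.1.1: serious adverse experiences "must be reported promptly to the Principal Investigator".
- Section 5.3: the Step 3 regimen follows national guidelines "or as directed by the Principal Investigator or designee".

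**The concern.** In an open-label trial, blinded classification by a committee is the main protection for endpoints that involve judgement. It works only if the people classifying a case do not know the arm. The protocol gives the chair to a role that its own procedures inform about individual patients' treatment. It states no separation of the chair from patient management, no recusal and no masking of case files.

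The stake is the clinical part of the primary composite and the TB relapse endpoint. For recurrent TB, section 6.2.6 settles disagreement by consensus after the members meet, and a chair who knows the arm could influence that discussion, even without intending to.

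**Working it through.** The protocol states no figure on this point. The check sets its provisions side by side.

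**1. Does a contact with the PI role reveal the arm?** Under section 5.2 and Table 4, before a primary outcome the punctuated arm takes ARV for six months and the delayed arm takes anti-TB drugs only. A decision to discontinue or restart ARV in that period therefore identifies a punctuated-arm patient. An SAE report can do the same: section 8.1.2.2.3 requires abacavir hypersensitivity to be reported as an SAE, and section 6.3.1.1 says nothing about masking reports sent to the PI. Knowledge gained this way persists when a later AIDS-defining condition or relapse is classified.

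**2. Can the contact coincide with the event to be classified?** Yes. Section 5.3 says that a patient who reaches a primary outcome while on punctuated therapy is evaluated for holding, discontinuing or restarting the regimen, and refers to section 8.1.4. For such a patient, the PI or designee can be consulted on the regimen around the event that the committee must classify.

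**3. Does another provision close the gap?** Section 11.4 keeps the PI blinded to interim data or analyses sorted by arm. That does not cover individual assignments.

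**4. Which outcomes are exposed?**

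| Outcome | Basis | Exposure |
| --- | --- | --- |
| CD4 component | Two values below 250 within three months; laboratory staff blinded (5.2.3, 6.1.1) | Largely insulated |
| Death | Fact of death (6.1.3) | Largely insulated |
| Stage 3 severe bacterial infection | Isolation from an ordinarily sterile site (6.1.2) | Small |
| Stage IV AIDS-defining condition | Definitive or presumptive criteria (5.3, Appendix II) | Exposed where presumptive |
| TB relapse | Only definite and probable cases count (6.2.6) | Exposed at the probable/possible line |
| Abacavir hypersensitivity | Uses the course after withdrawal (6.3.1.2.1) | Treatment visible whoever chairs |
| Paradoxical reaction, fever criterion | Onset after HAART starts (6.3.3) | Treatment visible whoever chairs |

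**5. How wide is the presumptive route?** Appendix II lists 22 Stage IV conditions, and 11 of them have no presumptive diagnosis. Section 6.1.2 excludes TB from staging, which removes extrapulmonary TB. That leaves 22 − 11 − 1 = 10 conditions with a presumptive route. For one of these, herpes simplex, the visceral form still needs a definitive diagnosis.

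**6. How sensitive is the relapse endpoint?** Section 10.2.2.2 expects relapse in 3% to 10% of patients: 0.03 × 350 = 10.5 and 0.10 × 350 = 35, which the protocol gives as 10 to 35 cases. One case moved across the probable/possible line is then 1/35 = 2.9% to 1/10 = 10% of all relapses. This shows that few cases carry the comparison; it does not estimate bias.

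**7. Size for the primary endpoint.** The protocol gives no expected split of primary events into CD4, clinical and death components, so no bias can be calculated.

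**The case against.** The strongest reply is that the protocol permits the overlap without requiring it. Section 6.0 allows a designee as chair and does not say which PI is meant. Section 8.1.4.2 accepts the U.S. or the on-site PI, or a designee. One PI could chair while the other handles the drug decisions. This stands. A reader might infer that the PI will chair and will know every patient's arm, and the documents do not support that. Decisions to hold drug rest with medical officers, their supervisors and study investigators. Only discontinuation and restart must go to a PI or designee, and patients with no such decision and no revealing SAE report are not exposed by these routes. In Step 3 both arms take ARV, so a later decision does not by itself identify the arm.

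A reader might also infer that the primary result as a whole is unprotected. That goes too far. CD4 events rest on blinded laboratory measurement, half of the listed Stage IV conditions have no presumptive route, committee members come from three institutions, and recurrent TB is classified against standard criteria with no casting vote for the chair.

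A third tempting inference is that a new chair would make all classification blinded. It would not: abacavir hypersensitivity and the fever criterion depend on treatment by definition.

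Finally, section 9.1 promises a manual of operations, which may hold masking and recusal procedures. That is possible, and their absence from the protocol does not show that they do not exist. The point concerns what section 6.0 itself fixes: a chair whose role can conflict with the blinding claimed in the same sentence.

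**Conclusion.** The point holds in limited form. The protocol claims blinded classification of all outcomes but allows the committee to be chaired from a role that can learn the arm of some patients before their outcome is classified. For those patients the stated blinding is not secured. The exposure lies mainly in AIDS-defining conditions accepted on presumptive criteria and in the probable/possible line for TB relapse. Neither the number of patients affected nor the size or direction of any bias can be derived from the protocol.

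The conclusion assumes that the chairing PI or designee is, or confers with, the person consulted on ARV decisions or receiving SAE reports. It also assumes that no unseen manual or charter separates these roles. This is a minor weakness that is cheap to remove, and it does not by itself put the primary comparison in doubt.

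**What to change.** 1. In section 6.0, replace the words that give the chair to the PI or designee with: *chaired by a committee member with no role in patient management, SAE review or ARV decisions*.
2. Add a recusal rule: anyone who managed a patient, or was consulted on that patient, does not vote on that case.
3. State that arm and ARV information is removed from case files wherever the outcome definition allows.
4. In section 5.2.3, state that abacavir hypersensitivity and the post-HAART fever criterion for paradoxical reactions cannot be classified fully blinded.

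The cost is small. The committee already draws on three institutions and a designee is already allowed, so a suitable chair should be available. The PI gives up the chair, and case files need a little preparation. No endpoint definition, sample size or clinical rule changes.

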## 6.1 HIV Disease Progression

The main outcome of the study will be progression of HIV disease. Disease progression will be defined as the time interval from enrollment until one of the three following events, whichever occurs first: CD4+ count decline to two values less than 250/*µ*L within a three month time period, development of an AIDS-defining condition, or death.

### 6.1.1 Decline in CD4+ Lymphocyte Counts

The CD4+ T cell number will be monitored regularly during the study. When a CD4+ count is found to be below 250 cells/ml, the test will be repeated within one month because of inherent variability in CD4+ count. When any two values are below 250 cells/mL within a three month time period, then the patient will be considered to have reached a study outcome. The date from the first of these two values drawn within the 3 month window will be used in the analysis. CD4+ count is chosen as the primary outcome because it remains the best single immunologic marker for the risk of opportunistic infection.

### **6.1.2 AIDS-defining Conditions**

Patients will be evaluated regularly by medical officers for inter-current HIV-associated conditions**.** When a patient develops one or more WHO Stage 4 AIDS defining conditions, or a definitive diagnosis of a severe bacterial infection that meets WHO Stage 3 classification, that patient will be considered to have reached a study outcome. A modified version of the WHO Staging system for HIV Infection will be used to define presumed and confirmed inter-current conditions (Appendix II). The staging system in this study will exclude TB from the definitions given; that is, patients will be staged according to infections or conditions other than TB. Definitive diagnosis of a WHO Stage 3 severe bacterial infection requires isolation of bacteria from an appropriate clinical specimen from an ordinarily sterile site.

### **6.1.3 Death**

Death and date of death will be obtained from family members and caregivers through standard verbal autopsy and local hospitals (death certificate and autopsy reports). If the date of death is not known or cannot be ascertained through medical records, it will be assigned a value of the 15th in the month death occurred. All deaths will be reported as serious adverse events.

##

## 6.2 Response to Antituberculosis Therapy

### **6.2.1 Sputum Culture Conversion**

The proportion of patients with MTB sputum conversion (from positive to negative) per treatment group will be determined at months 1 and 2. For an individual patient, sputum culture conversion will be defined as the absence of mycobacterial growth on solid media without a subsequent positive sputum culture during the first 16 weeks of therapy. Subjects with all sputum cultures negative at 2 consecutive time points who are clinically stable or improving and unable to produce sputum will be considered to have converted their sputum at the date of the first of the two specimens. Patients with one negative sputum culture after a period of treatment, who are clinically stable or improving and unable to produce sputum thereafter, will be considered to have converted their sputum culture at the time of the first specimen.

**6.2.2** **Completion of Antituberculosis Therapy**

Patients who take two months of isoniazid, rifampin, pyrazinamide, and ethambutol AND four months of isoniazid and rifampin will be classified as completing a course of antituberculosis therapy. Effective antituberculosis therapy is defined as a regimen in which the organism is susceptible to two or more antituberculosis agents.

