### **5.1.1 Standard First Line Antituberculosis Therapy**

#### **5.1.1.1 Drug Regimens, Administration and Duration**

All patients will receive standard short-course antituberculous therapy recommended by the Centers for Disease Control and Prevention and the World Health Organization. This treatment includes isoniazid, rifampin, and pyrazinamide and ethambutol for two months followed by isoniazid and rifampin for four months (2RHZE/4RH). Rifabutin will not be substituted in this study because it is not currently available in Uganda. Furthermore, given the limited use of rifabutin in Africa, the generalizability of the study will be increased with the use of rifampin. A patient is considered to have completed therapy when the six month, standard short-course antituberculosis treatment is taken with demonstrated clinical or bacteriologic response to treatment.

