### **6.2.5 Treatment Failure**

A culture-positive treatment failure is defined as a patient who is receiving anti-TB treatment and has at least one sputum mycobacterial culture growing at least 5 colonies of *M. tuberculosis* (MTB) on solid medium after completing 4 or more months of effective anti-TB treatment. Patients who default before completing anti-TB treatment and return later with culture-positive tuberculosis will be termed failures after non-adherence.

Patients will be retreated in accordance with applicable national TB program guidelines and drug susceptibility testing results.

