### **6.2.6 Relapse of Tuberculosis**

A relapse case of tuberculosis is defined as incident tuberculosis that develops in a patient who completed a course of antituberculosis treatment AND had clinical and/or microbiologic evidence for response to treatment in the earlier episode. Relapse cases may be defined as either clinical or culture-confirmed relapses.

- A clinical relapse is defined as a patient with clinical and/or radiographic evidence of recurrent tuberculosis not confirmed by a positive mycobacterial culture during follow-up after successful completion of initial anti-TB treatment (defined in 6.2.2).

- A culture-confirmed relapse is defined as a patient with clinical and/or radiographic evidence of recurrent tuberculosis that is confirmed with one or more positive cultures for mycobacterial growth. A mycobacterial culture is considered positive as follows: 1) a mycobacterial culture has at least 5 colonies of *M. tuberculosis* (MTB) on solid medium; 2) a mycobacterial culture

growing fewer that 5 colonies of MTB on solid medium with the same RFLP pattern as strain causing initial disease; or 3) mycobacterial growth detect using BACTEC.

Clinical evidence of active tuberculosis includes clinical signs (cough, consolidation, lymphadenopathy, wasting, fever, meningitis, ascites, etc.) and symptoms (cough, fever, weight loss, anorexia, headache, abdominal distention, etc.). Radiographic evidence includes an abnormal chest X-ray with findings consistent with TB.

In some unusual instances, positive mycobacterial cultures are found in patients without signs or symptoms of active TB in whom routine screening is performed. In these cases, patients with isolated single positive sputum cultures will not be considered to be relapses unless, as described above, they have signs or symptoms consistent with active tuberculosis and respond to antituberculosis treatment. For patients without signs or symptoms who have multiple positive cultures, these patients will be considered probable cases.

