## Tuberculosis

### **8.2.1 Tuberculosis Disease Management**

All patients will receive standard short-course antituberculous therapy recommended by the Centers for Disease Control and Prevention and the World Health Organization. This treatment includes isoniazid, rifampin, and pyrazinamide and ethambutol for two months followed by isoniazid and rifampin for four months (2RHZE/4RH, hereafter RHZE). Isoniazid will be given at a dosage of 300 mg per day. The daily doses of rifampin, ethambutol, and pyrazinamide will be adjusted according to body weight. For subjects weighing less than 50 kg, the daily doses will be rifampin 450 mg, pyrazinamide 1.5 gm, ethambutol 800 mg; for subjects weighing 50 kg or more, the daily doses will be rifampin 600 mg, pyrazinamide 2 gm, and ethambutol 1200 mg.

In Uganda, it has been estimated that 8% of MTB isolates from selected patients are resistant to isoniazid and 11% resistant to streptomycin. Multi-drug resistance, that is drug resistance to isoniazid and rifampin, is uncommon in Uganda at this time; in the course of evaluating over 500 TB cases in the past 5 years, we have identified only 3 cases of multi-drug resistant TB (MDR TB). All study patients will have drug susceptibility testing done at baseline so that results are available within two months. Participants with MDR TB will discontinue study participation and will be referred to the Tuberculosis Clinic where they will receive appropriate treatment for MDR TB and HIV infection. Appropriate treatment for MDR TB will be selected using drug susceptibility testing of isolates**.**

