Isoniazid (INH), the hydrazide of isonicotininc acid, was introduced into TB treatment in 1952. Its antimicrobial activity is limited to mycobacteria where it inhibits the synthesis of mycolic acids, key components of the mycobacterial cell wall. INH is acetylated in the liver. Seventy-five to 95% is excreted as inactive metabolites in the urine. The incidence of adverse reactions to INH is approximately 5%. Rash (2%), fever (1.2%), jaundice (0.6%), and peripheral neuropathy (0.2-2%) are the most frequent adverse reactions66. Rare adverse events include neutropenia, thrombocytopenia, seizures, encephalopathy, anti-nuclear antigen (ANA) positive small vessel vasculitis, dyspepsia, red cell aplasia, optic neuritis, methemoglobinemia, urinary retention and pellagra66. Severe and rarely fatal hepatitis may occur during INH treatment. The risk of hepatitis increases with age. In an earlier USPHS study, 1.3% of 12, 828 persons receiving INH preventive therapy were reported to have drug-related hepatitis67. No cases of INH-hepatitis occurred in persons less than 20 years old compared to 0.3% of those aged 20-34 years, 0.12% of those aged 35-49 years and 0.23% of those between 50 and 54 years. Eight (0.06%) fatalities occurred in this study. More recently, significant hepatotoxic reactions occurred in only 0.1% of over 11,00 consecutive individuals receiving clinically monitored INH preventive therapy at a U.S. public health clinic68.

Elevations of serum aminotransferases occur in 10-20% of all patients receiving INH. These increases developing during the initial weeks of therapy are generally asymptomatic and usually resolve despite continuation of the drug. Persons who consume ethanol (especially on a daily basis), those with pre-existing liver disease, and possibly pregnant and post‑partum women are at increased risk for hepatotoxicity. INH hepatotoxicity usually is reversible if the medication is stopped when initial symptoms occur.

In the event of INH hepatotoxicity (Grade III or greater), INH will be withdrawn until the hepatitis resolves when it will be reintroduced at a lower dose and escalated as tolerated. If hepatotoxicity recurs, substitution with a fluoroquinolone (Levofloxacin) will be made if the toxicity occurs during the first two months of treatment; thereafter ethambutol will be substituted.

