#### **10.2.2.2 Specific Aim 2**

To determine whether a punctuated six-month course of ARV therapy during treatment of active TB will improve the response to antituberculous therapy, as measured by one month culture conversion, treatment failure, and relapse TB, among patients with active TB and CD4+ cell count above 350 cells/µL.

The analysis of this Specific Aim will include only patients with active TB that have been randomized in the clinical trial. The effect of ARV treatment on the response to antituberculous therapy will be evaluated by comparing the proportion of subjects with negative smears or cultures at one and two months (chi square test). A similar analysis will be performed for antituberculosis treatment failure in the ARV treatment arms compared to the reference arm.

Previous published studies of TB in HIV infection estimate relapse rates between 3 and 10%; we thus expect to identify between 10 to 35 relapse cases of TB during the study. The cumulative incidence of TB relapse will be estimated by group using Kaplan-Meier methods; incidence density methods will also be used to measure the number of relapses per 100 person-years of observation after completing antituberculous treatment according to ARV treatment group. The incidence density ratio (95% confidence interval) will be estimated to compare incidence in treated and reference groups. Cox regression analysis will be used to determine whether punctuated ARV therapy is associated with relapse after adjusting for covariates. The analysis will account for the different treatment histories by using time-dependent Cox proportional hazards analysis. The analysis will be further stratified according to relapses due to reactivation and reinfection based on the RFLP patterns.

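### TB treatment completion is defined by the exact drugs 2HRZE/4HR, so a patient given a protocol-permitted substitution cannot be a clinical cure or a relapse

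*Protocol*

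**What the plan says.** **Completion.** Section 6.2.2 sets the rule by drugs and months: "Patients who take two months of isoniazid, rifampin, pyrazinamide, and ethambutol AND four months of isoniazid and rifampin will be classified as completing" a course. Section 5.1.1.1 gives a second version: "A patient is considered to have completed therapy when the six month, standard short-course antituberculosis treatment is taken", and adds a condition of clinical or bacteriologic response that 6.2.2 lacks. Neither mentions a substituted drug.

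**What depends on it.** Clinical cure (6.2.4) cites 6.2.2. Relapse (6.2.6) is "incident tuberculosis that develops in a patient who completed a course of antituberculosis treatment" with evidence of response, and its clinical-relapse item cites 6.2.2 by number. Section 10.2.2.2 counts "relapses per 100 person-years of observation after completing antituberculous treatment".

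**What does not depend on it.** Microbiologic cure (6.2.3) rests on cultures alone. Treatment failure (6.2.5) needs a positive culture in a patient on treatment "after completing 4 or more months of effective anti-TB treatment". Section 6.2.2 explains the term: "Effective antituberculosis therapy is defined as a regimen in which the organism is susceptible to two or more antituberculosis agents".

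**Departures the protocol provides for.** Under 8.2.2.1, a drug whose toxicity recurs on restart is stopped for good and a second-line agent added. For recurrent isoniazid hepatotoxicity, 8.2.2.2 says "substitution with a fluoroquinolone (Levofloxacin) will be made if the toxicity occurs during the first two months of treatment", and that ethambutol is used after that. Section 8.2.3.3 allows a second-line substitute instead of a restart. The audit tool in Appendix VII asks whether an alternate regimen was recorded for patients resistant to any standard TB drug. Only multi-drug-resistant patients leave the trial (4.4, 8.2.1).

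**The concern.** The completion rule and the substitution rules do not fit together. A patient managed exactly as section 8.2 provides can take a full course and still not be a completer. That patient then cannot be a clinical cure or a relapse, and adds no person-time after completion.

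If TB recurs a year later, no outcome category takes the event. It is not a relapse under the opening definition of 6.2.6, because the course was not completed. It is not a failure, because the patient is no longer on treatment. It is not a failure after non-adherence, because there was no default.

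At stake are the Aim 2 comparisons of cure and relapse. Completer status is settled after randomization, and drug toxicity can change it. The protocol gives reasons why this might differ by arm: ARV agents are linked to changes in liver function (1.1.2), abacavir hypersensitivity may be confused with rifampin side effects (6.3.1.2.1), and all potential causative agents are held for grade III or IV events (8.1.2.1.2).

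**Working it through.** **1. The plan's own figure.** Section 10.2.2.2 expects 10 to 35 relapses from rates of 3% to 10%. With N = 350 (10.1): 350 × 0.03 = 10.5 and 350 × 0.10 = 35. The figure reproduces.

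**2. Which outcomes remain open.** R, H, Z, E and L stand for rifampicin, isoniazid, pyrazinamide, ethambutol and levofloxacin. In row B, levofloxacin is assumed to continue with rifampicin in the last four months. An agent is active if the strain is susceptible to it.

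| Patient | Active agents, months 1–2 then 3–6 | Completer under 6.2.2 | Relapse or clinical cure possible | Failure possible |
|---|---|---|---|---|
| A. Susceptible, 2HRZE/4HR | 4, then 2 | Yes | Yes | Yes |
| B. Susceptible, H replaced by L early | 4, then 2 | No | No | Yes |
| C. Susceptible, H replaced by E after month 2 | 4, then 2 | No | No | Yes |
| D. H-resistant, 2HRZE/4HR | 3, then 1 | Yes | Yes | Depends on reading |
| E. H-resistant, moved to R plus E after month 2 | 3, then 2 | No | No | Yes |

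The completion rule removes rows B, C and E from relapse and clinical cure. It does not touch failure or microbiologic cure.

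**3. Row D.** If *effective* is judged by phase, this patient has 2 effective months, short of the 4 that failure requires. Judged over the whole course, three agents are active (R, Z, E) and the condition is met. The culture scheduled between weeks 18 and 20 of TB treatment (7.3.2) falls in the HR phase, so a positive result there is a failure on one reading and not on the other.

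**4. Size from substitution.** The protocol gives no substitution rate. Assume 1% to 5%. The upper value is the protocol's total isoniazid reaction rate (8.2.2.2), an upper limit for isoniazid substitutions; replacement of the other drugs is not counted separately.
- Patients: 350 × 0.01 = 3.5; 350 × 0.05 = 17.5.
- Relapses at equal risk: 3.5 × 0.03 = 0.1 at the low end; 17.5 × 0.10 = 1.75 at the high end.

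**5. Ceiling if isoniazid-resistant patients also change regimen.** Section 8.2.1 reports that "8% of MTB isolates from selected patients are resistant to isoniazid": 350 × 0.08 = 28 patients. If all 28 changed regimen, 28 × 0.03 = 0.8 to 28 × 0.10 = 2.8 relapses would be lost. With 5% substitution and no overlap (13%): 350 × 0.13 = 45.5 patients, and 45.5 × 0.03 = 1.4 to 45.5 × 0.10 = 4.6 relapses. Nothing in section 8.2 moves all resistant patients off the standard regimen, so this is a ceiling and not an estimate.

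**The case against.** The strongest reply is that the gap is minor and partly covered. The committee text that closes 6.2.6 sends every recurrence to blinded review and counts definite and probable cases as relapses, without repeating the completion condition. Only the clinical-relapse item cites 6.2.2 by number, and 10.2.2.2 does not cite it at all. Substitution should also be uncommon: for isoniazid hepatotoxicity the drug is first withdrawn and reintroduced, and it is replaced only if the toxicity recurs. These are secondary outcomes, and recurrent TB is excluded from the primary endpoint (Table 6, 6.1.2).

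The points on size and priority stand. The committee text does not close the gap. The opening definition of 6.2.6 still requires a completed course, so the section gives two rules for the same patient. Even if the committee rule prevails, clinical cure stays closed to that patient, and the start of post-completion person-time is undefined.

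A reader might go further and infer that isoniazid-resistant patients are shut out of relapse, clinical cure and failure alike, so that 28 patients are lost. The text does not support this. Completion depends on drugs taken, not on susceptibility, so a resistant patient who takes 2HRZE/4HR can be a relapse or a clinical cure. The failure gap for that patient exists only on the phase-by-phase reading. Isoniazid resistance is a property of the screening isolate, taken before randomization, so it is not itself a post-randomization loss.

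**Conclusion.** The point holds in a limited form. The completion definition contradicts the protocol's own substitution rules, and a patient treated as section 8.2 provides is misclassified for clinical cure, relapse and relapse person-time. Treatment failure and microbiologic cure are not affected by the completion rule. Separately, *effective* is ambiguous in a way that decides failure for isoniazid-resistant patients on the standard regimen.

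The effect is about 0.1 to 1.75 of the 10 to 35 expected relapses. This assumes 1% to 5% substitution and equal relapse risk, and it grows if some of the at most 28 isoniazid-resistant patients change regimen. A difference between arms is plausible because substitution follows toxicity, but the protocol gives no figure for it. The correction is worth making because the relapse comparison rests on few events and the remedy is cheap. Removing the *effective* condition from the failure definition is not warranted: counting failure only under adequate drug activity is a legitimate choice, provided the term is clear.

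**What to change.** - In 6.2.2, define completion as finishing the full course of the TB regimen prescribed under the protocol, including substitutions permitted under 8.2 or made because of susceptibility results.
- Bring 5.1.1.1, 6.2.4, both parts of 6.2.6 (the opening definition and the committee classification) and the person-time wording in 10.2.2.2 into line with that definition. Settle whether response to treatment is part of completion, since 5.1.1.1 and 6.2.2 differ on this.
- In 6.2.2 or 6.2.5, state whether *effective* is judged by phase or over the whole regimen.

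These changes concern how outcomes are classified and leave the choice of regimen alone. The cost is wording only, with no new data. The drawback is that the completer group becomes slightly more heterogeneous by regimen.
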